**ABBREVIATIONS:**

AACE = American Association of Clinical Endocrinologists;

CGM = continuous glucose monitoring;

CPT = Current Procedural Terminology;

CSII = continuous subcutaneous insulin infusion;

DM = diabetes mellitus;

FDA = US Food and Drug Administration;

HbA1c = glycated hemoglobin;

JDRF = Juvenile Diabetes Research Foundation;

SMBG = self-monitoring of blood glucose.

BGL = blood glucose levels.

**INTRODUCTION**

A continuous glucose monitoring system (CGMS) records data obtained from a subcutaneous sensor every 5 min for up to 72 hr and provides the clinician with a continuous profile of tissue glucose levels. The interstitial glucose levels lag approximately 15 min behind the blood glucose values at any given level. The CGMS values tend to have a high correlation coefficient for blood glucose values ranging between 40 and 400 mg/dL.

CGMS is minimally invasive and entails the placement of a small, subcutaneous catheter that can be easily worn by adults and children. CGM can be used in two clinical scenarios. First, being **retrospective(professional CGM)** recording of glucose, usually with integrated insulin infusion pump, for 48-72 hours for clinicians to analyze and further make recommendations for treatment to patients based on trends seen over those 48-72 hours. The system provides information that allows the patient and health care team to adjust the insulin regimen and the nutrition plan to improve glycemic control. CGMS can be helpful in detecting asymptomatic nocturnal hypoglycemia as well as in lowering HbA_1c_ values without increasing the risk for severe hypoglycemia.

Second, use is **real time continuous glucose monitoring (personal CGM)** usually with integrated insulin infusion pump, which helps patient have real time knowledge of his blood sugar values and their trends based on which patient can take action as regard to insulin dose. While there are potential pitfalls in CGMS use, including suboptimal compliance, human error, incorrect technique, and sensor failure, the implementation of CGMS in ambulatory diabetes practice allows the clinician to diagnose abnormal glycemic patterns in a more precise manner.

**Professional CGM**: Continuous glucose monitoring equipment is attached to patients with their consent and they remain unaware of monitoring results until they are downloaded and analyzed. Professional continuous glucosemonitoring has similarities to other methods of retrospective monitoring in medicine and has been called the “Holter-monitor of diabetes”.

**Personal CGM**: In personal real-time CGM, glucose values are visible continuously to the patient; this allows for immediate therapeutic adjustments based on “real-time” glucose results. It is usually used along with insulin pumps.

**Advantages of Professional Continuous glucose monitoring compared to Real time CGM:**

1. Patient behavior is not influenced, so results are unbiased and can be used for therapeutic recommendations, including changes in diet, activity and medications.
2. Easier for patients to use and requires minimal training and set up**.**
3. It is cheaper compared to real-time CGM.

**Indications for professional continuous glucose monitoring in children with Type 1 DM(1,2):**

1. Children undergoing change in their diabetes regimen.
2. Nocturnal hypoglycemia/dawn phenomenon.
3. Hypoglycemia unawareness.
4. Postprandial hyperglycemia.
5. Patients with discrepancies between HbA1c and SMBG.
6. Patients unable to achieve goal with SMBG.

**WHY THIS STUDY?**

It is well known that tight glycemic control delays long-term complications of type 1 DM (3). Frequent monitoring of blood glucose by finger pricks with a glucometer by self/parents is conventionally done to see glucose control and insulin dose adjustments. However, self-monitoring of blood glucose (SMBG) done 4 times a day (as recommended) does not give idea of glucose trends over 24 hours.

Continuous glucose monitors are being used in the west for over a decade now to know the glucose trends over 24 hours. Professional CGM provides blood glucose values every 5 mins and is usually placed over 72 hours to see glucose tends over 3 consecutive days. Its accuracy and reliability has been established in adults. But till now only a few studies have been done on professional CGM in paediatric population especially in children below 8 years of years of age. Further, there are conflicting results regarding the beneficial effect of professional CGM in children as seen in few studies previously done (4, 5, 6, 7). Role of Professional CGMS in reducing HbA1c in Indian children with Type 1 Diabetes has not been studied. It is important to know that such a costly intervention should be recommended in Indian children as it may further add to financial burden in these patients.

**REVIEW OF LITERATURE**

There are previously very few studies done on use of professional CGM to demonstrate its efficacy in tight glycemic control and in reducing HbA1c levels. These are summarized in following table 1. Studies done on utility of Professional CGMS in adults and pregnant women are summarised in Table 2 and 3 respectively.

**Evidence for use of Real Time CGMS in Type 1 Diabetes**

1. A Cochrane review on “Continuous glucose monitoring systems for type 1 diabetes mellitus”,to assess the effects of CGM systems compared to conventional self-monitoring of blood glucose (SMBG) in patients with diabetes mellitus type 1 has been recently published. Twenty-two RCTs meeting the inclusion criteria of this review were identified. The results of the meta-analyses (across all age groups) indicate benefit of CGM for patients starting on CGM sensor augmented insulin pump therapy compared to patients using multiple daily injections of insulin (MDI) and standard monitoring blood glucose (SMBG). After six months there was a significant larger decline in HbA1c level for real-time CGM users starting insulin pump therapy compared to patients using MDI and SMBG (mean difference (MD) in change in HbA1c level -0.7%, 95% confidence interval (CI) -0.8% to - 0.5%, 2 RCTs, 562 patients, I2=84%). The risk of hypoglycaemia was increased for CGM users, but CIs were wide and included unity (4/43 versus 1/35; RR 3.26, 95% CI 0.38 to 27.82 and 21/247 versus 17/248; RR 1.24, 95% CI 0.67 to 2.29).

For patients starting with CGM only, the average decline in HbA1c level six months after baseline was also statistically significantly larger for CGM users compared to SMBG users, but much smaller than for patients starting using an insulin pump and CGM at the same time (MD change in HbA1c level -0.2%, 95% CI -0.4% to -0.1%, 6 RCTs, 963 patients, I2=55%). On average, there was no significant difference in risk of severe hypoglycaemia or ketoacidosis between CGM and SMBG users. The confidence interval however, was wide and included a decreased as well as an increased risk for CGM users compared to the control group (severe hypoglycaemia:36/411 versus 33/407; RR 1.02, 95% CI 0.65 to 1.62, 4 RCTs, I_2_=0% and ketoacidosis: 8/411 versus 8/407; RR 0.94, 95% CI 0.36 to 2.40, 4 RCTs, I_2_=0%).

**Table 1 - Studies previously done on PROFESSIONAL CGM in children with type 1 Diabetes:**

| First author, year | Patients | Baseline HbA1c | Age group years | % male | No.  CGM | No. Control | CGM duration of use | CGM  frequency  of use | SMBG description | Type of study | Results | Conclusion |
| --- | --- | --- | --- | --- | --- | --- | --- | --- | --- | --- | --- | --- |
| Yates, 2006(4) | Children, T1DM | 8.2% CGM  7.9% Control | 13-15 | 36 | 19 | 17 | 3 days | 3 days  every 3  weeks for  a 3 month  period | Four to six times daily finger stick testing | Randomised control study | there was no difference in the degree of improvement in A1C at 12 weeks betweenthe CGMS (-0.4% [95% CI -0.7 to -0.1]) and the control group (-0.4% [-0.8 to 0.2]). | CGMS was no more useful than intermittent finger stick SMBG. |
| Lagarde, 2006(8) | Children, T1DM | 8.4% interven-  tion  8.8% control | 7-17 | 44 | 18 | 9 | 3 days | At 0, 2,  and 4  months | Finger stick with BD logic 4 times/day glucometer with once weekly measure at 2 AM | Single blind randomised control trial | The decrease in HbA1c of (0.61 +_ 0.68%) in the  intervention group was statistically significant (p = 0.03), whereas the  decrease in HbA1c of (0.28 +_ 0.78%) in the control group.was not. | Use of CGMS improves metabolic control in children with type 1 DM. |
| Deiss, 2006(9) | Children, T1DM | Arm A 7.8%  Arm B8.4% | 7 - 11 | 53 | 15 | 15 | 3 days | Twice  (once  blinded,  once  unblinded) | Accu-Chek with finger sticks at least five times daily | Randomised controlied cross-over trial | No significant change of HbA1c occurred within each arm (A,p = 0.183 and B, p = 0.823), rrespectively whether CGMS datawere blinded or not. Likewise, mean glucose and hyper- or hypoglycaemiavalues did not change significantly. | use of CGMS in children with  type 1 diabetes did not result in a significant improvement of  metabolic control. |
| Ludvigson, 2003  (10) | Children, T1DM | 7.7% CGM, 7.75% control | 9-15 | Not provided | Total 27 (cross over study) | Total 27 (crossover study) | 3 days | 3 days  every 2  weeks | SMBG at least two times in a day and seven times in a day once a week | A controlled cross-over study | HbA1c decreased significantly in open-arm (from 7.70%-7.31%)but not in blind arm (7.75-7.65%). | CGMS a useful tool for education and improving metabolic control. |
| Chase, 2001(11) | Children, T1DM | 10% CGM  9.0% control | 10-17 | 55 | 5 | 6 | 3 days | Anytime  within the  30- day  Period | 4 times/day | Randomised control trial | CGMS, the 5 children had a significantly lower mean  HbA1c value compared with their initial value (mean 6standard error of the mean [SEM] decrease 5 (.36% +-.07%). The mean decrease for the controls was (.2%+-.2%). | CGMS allows recognition of nocturnal hypoglycaemia. |

**Table 2. Randomized Controlled Clinical Trials Evaluating the Effects of Continuous Glucose Monitoring in the Treatment of Type 1 Diabetes Mellitus**

|  | **Trial Name** | **Description** | | **Outcomes** | |
| --- | --- | --- | --- | --- | --- |
| Adults and adolescent | **STAR-1 (12)** | Primary end point: HbA1c  change from baseline  Also evaluated  hyperglycemia and/or  hypoglycemia incidence  Evaluated CSII patients 12 to  72 years of age | | 6-Month HbA1c (vs baseline HbA1c 8.44%)  CGM + SMBG-treated patients: 7.77%  SMBG patients: 7.84%  Patients with ≥60% sensor utilization compliance experienced  significant HbA1c reduction compared with less-compliant  patients (*P*<.05)  Severe hypoglycemia rates were higher in the CGM group^a^ | |
|  | **JDRF(13)** | Primary end point: HbA1c  change from baseline in CSII  and MDI patients  Also evaluated hypoglycemia  incidence  Evaluated patients 15 to 24  and ≥25 years of age (adult  groups) | | 26-Week HbA1c (vs baseline):  Age 15 to 24 years (baseline HbA1c 7.9%-8.0%)  Mean HbA1c difference of 0.08% for CGM + SMBG  patients vs SMBG alone^b^  Age ≥25 years (baseline HbA1c 7.6%)  Mean HbA1c difference of – 0.53% for CGM + SMBG  patients vs SMBG alone^a^  Severe hypoglycemic events were rare and occurred at the same rate for both study groups; both study groups also demonstrated similar biochemical hypoglycemia rates  Patients aged ≥25 years showed increased sensor use compared with other patients  Frequency of CGM monitoring was associated with  significantly greater HbA1c reductions in all study groups | |
| ***Key takeaway: More consistent CGM use predicts HbA1c reductions*** | | | | | |
| Youth | **DirecNet(14)** | | Two, 13-week pilot studies  (DirecNet); randomized  clinical trial (JDRF CGM)  Primary end point: HbA1c  change  Safety end point:  Hypoglycemia incidence | | HbA1c among CSII users improved from 7.1% at baseline to  6.8% at 13 weeks^a^  Hypoglycemia frequency changed from 4.5% at baseline to  5.5% at 13 weeks^b^ |
|  | **JDRF CGM(13)** | |  |  | After 26 weeks, HbA1c levels <7% in 27% of CSII users vs 12%  of control group (age 8-14 years)^a^  Patients who used the sensor 6 to 7 days a week were able to  lower their HbA1c level by a mean of 0.8% and maintain this  improvement for 12 months  Hypoglycemia rates did not differ between treatment groups |
| ***Key takeaway: Youth were much less likely than adults to use CGM devices on a near-daily basis; the best HbA1c-lowering***  ***results were seen in patients who used the sensor 6 to 7 days a week*** | | | | | |

Abbreviations: CGM, continuous glucose monitoring; CSII continuous subcutaneous insulin infusion; DirecNet, Diabetes Research in Children Network; HbA1c, hemoglobin A1c; JDRF, Juvenile Diabetes Research Foundation Sensor Study; MDI, multiple daily injections; SMGB, self-monitoring of blood glucose; STAR-1, Sensor-augmented pump Therapy for A1C Reduction.

a Statistically significant.

b Not significant.

**Table 3.Studies evaluating the efficacy of professional continuous glucose monitoring in pregnant women with diabetes mellitus.**

| Study | Goal | Patients | Duration | Intervention | Outcomes |
| --- | --- | --- | --- | --- | --- |
| Jovanovič  (2000) (15) | Evaluate professional CGM  to detect previous unknown  hyperglycemia in women  with GDM | 10 women with GDM  (no gestational data  provided) | 72 hours | Professional CGM | Mean total min/24 h previously  undetected hyperglycemia:  ~30 min |
| Yogev et al  (2003) (16) | Comparison of daily  glycemic profiles in  pregnant women with type  1 DM measured by  professional CGM vs  intermittent glucose  monitoring | 34 pregnant women with  type 1 DM, gestational  age 16 to 32 weeks,  receiving multiple  insulin injections | 72 hours | Professional CGM  Vsfingerstick  glucose  measurements  performed 6 to 8  times a day | Average of 780 ± 54 glucose  measurements recorded for  CGM patients; mean total  hyperglycemia in professional  CGM arm (undetected by  fingerstick): 192 ± 28 min/24  h; nocturnal hypoglycemic  events recordedin a total of 26  patients |
| Chen et al  (2003) (17) | Evaluate daily glucose level  in pregnant women with  GDM using professional  CGM vs SMBG | 57 women with GDM,  gestational age 24 to  35 weeks; 23 treated  by diet alone, 34 by  diet and insulin | 30 days | Professional CGM  vs SMBG with  fingerstick | Average of 763 ± 62 glucose  measurements recorded for  CGM patients; mean total  hyperglycemia (undetected by  fingerstick): 132 ± 31 min/24 h  in insulin-treated group and 94  ± 23 min/24 h in diet-treated  group; 14 patients, all insulin treated,  experienced nocturnal  hypoglycaemia |
| Murphy et al  (2008) (18) | Evaluate the effectiveness of  professional CGM during  pregnancy on maternal  glycemic control, infant  birth weight, and risk  of infant macrosomia in  women with type 1 DM  and type 2 DM | 46 women with type 1  DM and 25 women  with type 2 DM,  gestational age 8 to  32 weeks | 3 years | Antenatal care  plus professional  CGM (n = 38)  or standard  antenatal  care (n = 33);  professional  CGM offered for  ≤7 days every 4  to 6 weeks | Patients using professional CGM  had lower mean hemoglobin  A1c levels (5.8% vs 6.4%);  infants of CGM-using women  had decreased median birth  weight percentiles (69% vs  93%) and a reduced risk of  macrosomia (odds ratio 0.36;  95% CI, 0.13-0.98; *P* = .05) |

Health-related quality of life was reported in five of the 22 studies. In none of these studies a significant difference between CGM and SMBG was found. Diabetes complications, death and costs were not measured. Authors concluded that there is limited evidence for the effectiveness of real-time continuous glucose monitoring (CGM) use in children, adults and patients with poorly controlled diabetes. The largest improvements in glycaemic control were seen for sensor-augmented insulin pump therapy in patients with poorly controlled diabetes who had not used an insulin pump before. The risk of severe hypoglycaemia or ketoacidosis was not significantly increased for CGM users, but as these events occurred infrequent these results have to be interpreted cautiously.There are indications that higher compliance of wearing the CGM device improves glycosylated haemoglobin A1c level (HbA1c) to a larger extent (19).

2. Meta- analysis was conducted by Szypowska A et al, to explore the potential beneficial effects of the use of RT-CGM on diabetes management compared with self-blood glucose measurement (SBGM) in patients with type 1 diabetes. Seven RCTs (total patients- 948) met their inclusion criteria. Meta- analysis showed better HbA1c reduction in subjects using RT-CGM compared with those using SBGM (mean difference (MD) being - 0.25;95%confidence interval (95%CI): from -0.34 to -0.17;P<0.001).Patients treated with insulin pump and RT-CGM had a lower HbA1c level compared with subjects managed with insulin pump and SBGM (four RCTs, n =497; MD - 0.26; 95% CI: from -0.43 to -0.10; P<0.002). The benefits of applying RT-CGM were not associated with an increasing rate of major hypoglycemic episodes. The use of RT-CGM for over 60–70% of time was associated with a significant lowering of HbA1c.Authors concluded that RT-CGM is more beneficial than SBGM in reducing HbA1c in patients with type 1 diabetes. However, suggested that further studies are needed to evaluate the efficacy of this system in the pediatric population, especially in very young children as number of children in studies analysed was very less (20).

3**.** Another meta-analysis by Golden SH et al including 41 RCTs (including adults and children with either type1 or type 2 DM) showed that in children and adults with type 1 diabetes, CSII use was associated with improved quality of life compared with MDI (low SOE). They found studies of the comparative effectiveness of RT-CGM versus SMBG in individuals with type 1 diabetes only. Compared with SMBG, RT-CGM achieved a lower HbA1c, with greater reductions occurring where sensor compliance was 60 percent or greater (high SOE). There was no difference in the rate of severe hypoglycemia (low SOE) or quality of life (low SOE).They concludedthat RT-CGM is superior to SMBG in lowering HbA1c, without affecting the risk of severe hypoglycemia, in individuals with type 1 diabetes, particularly when compliance is high. Sensor-augmented pumps are superior to MDI/SMBG in lowering HbA1c (21).

4. In a meta-analysis to review how intensive insulin therapy (multiple daily injections [MDI] vs. rapid-acting analogue -based continuous subcutaneous insulin infusion [CSII]) or method of monitoring (self-monitoring of blood glucose [SMBG] vs. real-time continuous glucose monitoring [rt-CGM]) affects outcomes in type 1 and 2 diabetes mellitus, 33 randomized controlled trials in children or adults that compared CSII with MDI (n = 19), RT-CGM with SMBG (n = 10), or sensor-augmented insulin pump use with MDI and SMBG (n = 4) were included of analysis. Results revealed that MDI and CSII had similar effects on hemoglobin A1c (HbA1c) levels and severe hypoglycemia in children or adults with type 1 diabetes .Compared with SMBG, RT-CGM achieved a lower HbA1c level (between-group difference of change, -0.26% [95% CI, -0.33% to -0.19%]) without any difference in severe hypoglycemia. Sensor-augmented insulin pump use decreased HbA1c levels more than MDI and SMBG did in persons with type 1 diabetes mellitus (between-group difference of change, -0.68% [CI, -0.81% to -0.54%]). Authors, thus, concluded that continuous subcutaneous insulin infusion and MDI have similar effects on glycemic control and hypoglycemia, except CSII has a favourable effect on glycemic control in adults with type 1 diabetes mellitus. For glycemic control, rt-CGM is superior to SMBG and sensor-augmented insulin pumps are superior to MDI and SMBG without increasing the risk for hypoglycemia (22).

5. In another meta-analysis to determine the clinical effectiveness of real time continuous glucose monitoring compared with self-monitoring of blood glucose in type1diabetes.Six trials were identified, consisting of 449 patients randomized to continuous glucose monitoring and 443 to self-monitoring of blood glucose. The overall mean difference in HbA1c for continuous glucose monitoring versus self-monitoring of blood glucose was −0.30% (95% confidence interval −0.43% to −0.17%) (−3.0, −4.3 to −1.7 mmol/mol).Continuous glucose monitoring was associated with a significant reduction in HbA1c percentage, which was greatest in those with the highest HbA1c at baseline and who most frequently used the sensors. Exposure to hypoglycaemia was also reduced during continuous glucose monitoring. The most cost effective or appropriate use of continuous glucose monitoring is likely to be when targeted at people with type 1 diabetes who have continued poor control during intensified insulin therapy and who frequently use continuous glucose monitoring (23).

6. Another meta-analysis of 19 trials to assess the efficacy of continuous glucose monitoring (CGM) in improving glycemic control and reducing hypoglycemia compared to self-monitored blood glucose (SMBG), showed that CGM was associated with a significant reduction in mean hemoglobin A1c [HbA1c; weighted mean difference (WMD) of -0.27% (95% confidence interval [CI] -0.44 to -0.10)]. This was true for adults with T1DM as well as T2DM [WMD -0.50% (95% CI -0.69 to -0.30) and -0.70 (95% CI, -1.14 to -0.27), respectively]. No significant effect was noted in children and adolescents. There was no significant difference in HbA1c reduction between studies of real-time versus non-realtime devices (WMD -0.22%, 95% CI, -0.59 to 0.15 versus -0.30%, 95% CI, -0.49 to -0.10; p for interaction 0.71) (24).

**AIMS AND OBJECTIVES**

**Primary objective:**

1. To assess efficacy of professional CGM (done over 3 days) along with self-monitoring blood glucose (SMBG) in improving glycemic control compared to SMBG alone.

**Secondary Objectives:**

1. To assess feasibility and acceptability of professional CGM in diabetic children between 2 to 8 years of age.

2. Efficacy of professional CGM in reducing hypoglycemic and hyperglycemic episodes.

**RESEARCH QUESTION:**

Whether in children with Type1 DM, professional CGM along with SMBG decreases HbA1c significantly over 4months when compared to SMBG alone?

**Hypothesis:** Professional CGM when combined with SMBG, improves HbA1c in Type1 diabetic children (2 to 8 years old) when compared to SMBG alone.

**MATERIAL AND METHODS**

**Setting**: Pediatric Diabetic clinic, Advanced Pediatrics Centre, Postgraduate Institute of Medical Education and Research, Chandigarh.

**Study Period**: July 2014 to Dec 2015

**Study Design:** Prospective**,** Open Label Randomized control trial.

**Subjects**:

Children with Type 1 Diabetes attending our Pediatric Diabetes Clinic, between the age group of 2-10 yrs, will be randomized into two groups; Professional CGM plus SMBG (intervention group/Cases) and SMBG alone (control group).

**Inclusion criteria**:

1. Children with a diagnosis of Type 1 DM for at least 6 month
2. Age between 2 to 10 years.

**Exclusion Criteria**:

1. Children with history of acute metabolic decompensation such as DKA within previous 2 months.
2. Children on chronic medications known to affect blood glucose such as systemic corticosteroids.
3. Patients with known poor compliance and HbA1c >12%.
4. Associated co-morbidities like Celiac disease and Hypothyroidism.

**Randomization and allocation concealment:** Participants will be randomized to intervention (Professional CGMS+SMBG) or control (SMBG alone) arms in equal numbers. Randomization will be done using computer generated random number list. Group allocation will be concealed with opaque sealed envelopes.

**Sample Size**: With a 1:1 randomization ratio and based on the assumption of a common SD of 1.5%, an absolute difference of 1% in HbA1c between study groups can be detected with an alpha error of 0.05 (two sided) and a beta error of 0.20, using formula n= 2 x K x SD^2^ /delta ^2^ (where K is constant, SD is standard deviation and delta is magnitude of difference to be detected). Sample size of 34 participants each in the intervention and control group will be required.

**Statistical analysis:**Baseline characteristics will be calculated as means and SD. Results will be presented as means (95% CI).Statistical significance will be set at P<0.05. The primary endpoint will be the unit change in HbA1c over 4 months from intervention. Secondary end points will be percentages of low (<70) and high (>200) sugar records of the total sugar records (SMBG). Continuous variables will be compared using a two-sided *t* test or paired *t* test for change within each subject/group before and after intervention (Professional CGM). Intergroup comparisons of HbA1c will be made using a signed-rank test. Univariate ANOVA will be used to examine factors that may confound the change in HbA1C. Data will be analysed using SPSS (SPSS Inc., Chicago, IL, version 18.0 for Windows).

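### The protocol's own formula and inputs give 36 per group (37 for a t test), not 34; on those inputs 34 gives 77% to 78.5% power, and no loss allowance is stated

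*Protocol*

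**What the plan says.** The Sample Size paragraph under Material and Methods gives every input needed to repeat the calculation.

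- Allocation: "With a 1:1 randomization ratio".
- SD and target difference: "based on the assumption of a common SD of 1.5%, an absolute difference of 1% in HbA1c between study groups can be detected".
- Error rates: "alpha error of 0.05 (two sided) and a beta error of 0.20".
- Formula: n = 2 × K × SD² / delta², "where K is constant, SD is standard deviation and delta is magnitude of difference to be detected". No value is given for K.
- Result: "Sample size of 34 participants each in the intervention and control group will be required".

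The Statistical analysis paragraph that follows defines the outcome: "The primary endpoint will be the unit change in HbA1c over 4 months from intervention". It names a two-sided t test for continuous variables. The Study Procedures section has children seen every two months for at least four months. The protocol states neither an expected loss rate nor an increase of the sample size for losses.

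**The concern.** Once alpha and beta are fixed, K is fixed, and the formula leaves no freedom in n. A stated n that does not follow from the stated inputs means that at least one of the quantities in the paragraph (K, SD, difference, power or n) is not what it is said to be. Because K is not given, a reader cannot tell which.

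The stated beta is at stake. A reader of the protocol or of the eventual report will take 80% power for a 1% difference as a property of the design, and may weigh a non-significant result accordingly. The absence of a loss allowance matters for the same reason: the endpoint needs an HbA1c at follow-up, and 34 leaves no margin even when every child provides one.

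**Working it through.** **Inputs**, all from the Sample Size paragraph: alpha = 0.05 two-sided, beta = 0.20, SD = 1.5, delta = 1, allocation 1:1.

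**1. The protocol's formula.**
K = (z for 0.975 + z for 0.80)² = (1.960 + 0.842)² = 7.849.
n = 2 × 7.849 × 1.5² / 1² = 4.5 × 7.849 = 35.3, rounded up to 36 per group (72 in total, against 68).

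**2. Can 34 be reached another way?**
- Rounding K: values of 7.8, 7.84, 7.85 and 7.9 give 35.1, 35.3, 35.3 and 35.6. All round up to 36.
- One-sided test: 28 per group.
- Two-sample t test, exact: 36.3, so 37 per group (74 in total).
- Working back: 34 / 4.5 = 7.56 is the K that gives 34. K depends on alpha and beta jointly. This value fits alpha 0.05 with beta 0.215, or beta 0.20 with alpha 0.0565, but not the stated pair.
- Keeping K = 7.849, exactly 34 needs an SD of 1.47 or a difference of 1.02.

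**3. Power with 34 analysed per group, on the stated inputs.**
Standard error of the difference = 1.5 × √(2/34) = 0.3638, and 1 / 0.3638 = 2.749.
Normal approximation: Φ(2.749 − 1.960) = Φ(0.789) = 78.5%.
Two-sample t test: 77.3%.
The shortfall from 80% is 1.5 or 2.7 percentage points. The difference detectable with 80% power is 1.02% (normal) or 1.03% (t test).

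**4. Losses.** The protocol gives no rate, so those below are assumptions. They apply only if 34 is the number enrolled.

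| Assumed loss | Mean analysed per group | t-test power, SD 1.5, difference 1 |
| --- | --- | --- |
| 0% | 34 | 77.3% |
| 5% | 32.3 | 75.1% |
| 10% | 30.6 | 72.7% |
| 15% | 28.9 | 70.2% |
| 20% | 27.2 | 67.5% |

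**5. Dependence on the SD.** The same t-test calculation with other SDs and a difference of 1:

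| SD | 34 per group | 20% loss (27.2 per group) |
| --- | --- | --- |
| 1.5 (stated) | 77.3% | 67.5% |
| 1.3 (illustrative) | 87.8% | 79.5% |
| 0.78 (see objection) | over 99% | over 99% |

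**The case against.** The discrepancy is slight. By the protocol's own formula, 34 per group loses 1.5 points of power, and the detectable difference of 1.02% rounds to the stated 1%. An SD of 1.47 would print as 1.5 and give 34. That stands as a matter of size: two or three children per group would not change how the trial is judged. It does not make 34 the result of the inputs as printed, and the protocol mentions no unrounded SD.

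The stronger objection concerns what follows. A reader might infer that the trial is underpowered. The documents do not support that, because the power figures hold only if 1.5% is the SD of the variable analysed. The protocol writes "based on the assumption of a common SD of 1.5" without saying whether this describes HbA1c or its change, while the endpoint is a change. In Table 1, one paediatric trial shows 0.68 and 0.78 beside its mean HbA1c decreases. If those are SDs of change and applied here, 34 per group would have over 99% power for a 1% difference, even after 20% loss. The protocol does not adopt those values, so they do not rescue the calculation, but they rule out an unconditional claim about power.

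A reader might also take 34 as the number to be randomised. The paragraph says only that 34 are required; it does not say whether that means enrolled or evaluable. The loss figures are therefore conditional on that reading as well as on assumed rates. What remains is that the protocol fixes a number with no margin and does not say which count it is.

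**Conclusion.** The point holds as a mismatch between stated inputs and stated result. Two-sided alpha 0.05, beta 0.20, SD 1.5%, difference 1% and equal allocation give 36 per group by the protocol's formula and 37 for a t test. Rounding K does not lead to 34, nor does a one-sided or t-test version of the calculation.

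With complete data the consequence is small: a shortfall of 4 to 6 children in total (68 against 72 or 74). The lack of a stated loss allowance can matter more, since an assumed 10% to 20% loss from 34 enrolled would bring power to about 73% to 67%. All of these figures are conditional on an SD of 1.5% for the analysed variable. The finding is that the stated power does not follow from the paragraph as written, not that the trial cannot detect a 1% difference. It should be corrected, and it does not call for a change of design.

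**What to change.** Keep 34 per group and restate the paragraph along these lines: *34 per group analysed gives about 77% power (two-sided 5% t test) for a 1% difference in HbA1c with SD 1.5%.* In the same paragraph:

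- give the value of K used;
- say whether 1.5% is the SD of HbA1c or of its change over 4 months;
- say whether 34 is the number enrolled or the number evaluable and, if enrolled, give the expected loss rate and the power that remains.

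The cost is one reworded paragraph and a slightly less favourable stated power; recruitment is unchanged. If the sponsor prefers to keep 80% as the headline, the stated inputs require 36 per group by the formula or 37 for a t test. With an assumed 10% loss these become 36 / 0.9 = 40 and 37 / 0.9 = 41.1, so 42 per group when rounded up.
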